### Patient selection and randomization

Patients will be enrolled into the trial according to the eligibility criteria (Table 1). Inclusion and exclusion criteria are based on the main selection criteria for patients with unresectable perihilar and/or ductal CCA who are recommended to receive bile duct stenting and palliative systemic therapy by current guidelines [2]. In detail, these criteria reflect the patient’s clinical status including potential safety concerns regarding the endoscopic intervention and administration of systemic chemotherapy. Performance status 0–1 according to the Eastern Cooperative Oncology Group (ECOG) is a well-established cut-off for the eligibility of patients to receive systemic therapy and invasive procedures, such as endoscopic retrograde cholangiopancreatography (ERCP). Patients will be excluded if prior RFA and/or multiple stenting for CCA has been performed during the past 3 months to rule out competing effects on the outcome analysis (first stent replacement or placement of the first stent for tumor-related bile duct obstruction within 3 months prior to study inclusion is allowed). Patients with concomitant diseases or malignancies with limited prognosis or high likelihood of study discontinuation (e.g. severe or uncontrolled cardiovascular disease, such as congestive heart failure New York Heart Association (NYHA) III or IV, unstable angina pectoris, myocardial infarction within ≤ 3 months, and/or significant arrhythmias) will be excluded. This is in line with clinical eligibility criteria for the administration of bile duct stenting and subsequent administration of systemic therapy. Taken together and considering a relatively large sample size and a multicenter study design, the study population is representative, and results are generalizable to the target population of interest.

**Table 1 Tab1:** Eligibility criteria for the ACTICCA-2 enrollment phase

Unresectable perihilar and/or ductal CCA with indication for bile duct stenting
Signed written informed consent
ECOG performance status 0–1
Age ≥ 18 years
Eligibility for palliative systemic therapy based on clinical and laboratory parameters (except hyperbilirubinemia) as determined by the local MDT
No prior RFA for CCA
No repeated bile duct stenting for > 3 months (trial inclusion is possible upon first stent replacement or initial stent placement)

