#### Screening

Within 3 weeks prior to randomization/start of first treatment (i.e. stenting with or without RFA) the following will be assessed/obtained:

Signed written informed consent.Medical history including previous cancer history, cancer treatment, concomitant diseases, current medication, prior endoscopic procedures.Demographics.ECOG performance status.Laboratory tests: Hematology panel (hemoglobin, platelets, WBC and WBC differential with neutrophils, lymphocytes, monocytes) chemistry panel (sodium, potassium, calcium, creatinine, total and direct bilirubin, alkaline phosphatase, 𝛾GT, ALT, AST, CrP, INR, aPTT, PT) and CA 19 − 9, CEA (optional).

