### Endpoint definition

The primary endpoint is time to first event, i.e. stent dysfunction defined by bilirubin > 5 mg/dl and/or cholangitis (fever > 38.5 °C and/or increase in C-reactive protein (CrP) by at least 3-fold upper limit of normal and at least 20% from baseline without extrahepatic focus and absence of tumor progression) leading to premature stent replacement and/or disruption of chemotherapy. This endpoint is clinically relevant and paramount for the management of patients with perihilar and/or ductal CCA and represents a generally agreed core outcome for this population. Because systemic treatment discontinuation due to biliary complications is so critical for these patients, these endpoints are proposed by current guidelines as surrogates for survival [2]. According to recently published studies on this topic, the event rate at 6 months in the control group is estimated to be 50% [14, 20]. Our study aims to detect a clinically relevant reduction of the rate by 50% in the RFA group to 25%, resulting in a number needed to treat (NNT) of 4. This event reduction has to be achieved in the setting of palliative systemic therapy and seems reasonable considering the previously reported beneficiary effects of RFA on stent patency and OS [7, 9, 14, 20]. Importantly, all possible events will be reviewed by a blinded and independent endpoint-review committee (ERC), leading to a prospective randomized open blinded endpoint (PROBE) design.

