### Sample size calculation and statistical analysis

The sample size of 120, i.e., 60 patients per group, was calculated based on the two-sided log-rank test for time to first event analysis. Thereby, a power of 80% can be reached under the following assumptions and with a two-sided significance level of 5%. Based on previous reports [7, 9, 14, 20], the event rate at 6 months in the control group was estimated to be 50% and 25% in the intervention group resulting in a hazard ratio (HR) of 0.415. The follow-up will be fixed at 6 months. Furthermore, it was assumed that there will be a low loss to follow-up of 2.5% over six months and all patients stay within their treatment group within the observational period. PASS version 16.0.3 was used for the calculation of the sample size.

Descriptive analysis for baseline characteristics will be performed giving mean, standard deviation, median, and inter-quantile range for continuous data as well as counts and percentages for categorical data. Tests of statistical significance will not be undertaken for baseline characteristics; rather the clinical importance of any imbalance will be noted [22]. A modified ITT (mITT) population will be used for the primary endpoint analysis. The mITT population consists of all patients who will be randomized in the ACTICCA-2 trial and who will undergo endoscopic stenting.

Primary endpoint analysis will be conducted using a cause-specific Cox proportional hazards model comparing the two treatment groups regarding time to first event within 6 months with trial site as random effect (frailty) and tumor location (perihilar vs. ductal) and stent material (plastic vs. metallic) as fixed effects. An adjusted HR for the treatment effect with corresponding 95% CI and p-value will be given as well as cumulative incidences with 95% CIs. The secondary endpoint OS will be analyzed with the Cox proportional hazards model with a frailty for trial site and adjusting for stratification variable tumor location and the variable stent material. Mixed models will be used for further secondary endpoints (linear, logistic, or negative binomial as appropriate).

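### The confirmatory Cox model does not adjust for baseline bilirubin, a value already scheduled in every patient; prespecifying it could add power at almost no cost, though the plan is valid without it

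*Protocol article*

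**What the plan says.** The section on sample size and statistical analysis specifies a cause-specific Cox model for the primary endpoint over the fixed 6-month follow-up. Besides treatment, its terms read: "with trial site as random effect (frailty) and tumor location (perihilar vs. ductal) and stent material (plastic vs. metallic) as fixed effects". This is the only confirmatory analysis. Randomization is stratified by site and tumor location. Stent material is therefore a covariate without being a stratum, and bilirubin is neither.

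Four other places bear on the point:

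- **Screening** lists "total and direct bilirubin, alkaline phosphatase" among the laboratory tests. Visit 1 repeats the tests if the screening values are more than 7 days old.
- **Table 1** sets as a criterion "Eligibility for palliative systemic therapy based on clinical and laboratory parameters (except hyperbilirubinemia) as determined by the local MDT", so raised bilirubin does not bar entry. No bilirubin limit is stated.
- **Endpoint definition** states: "The primary endpoint is time to first event, i.e. stent dysfunction defined by bilirubin > 5 mg/dl and/or cholangitis". The event must also lead to early stent exchange or to interrupted chemotherapy.
- **Baseline characteristics** are summarized without significance tests, and the clinical importance of any imbalance is to be noted.

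**The concern.** A patient's starting bilirubin plausibly predicts whether bilirubin later passes a fixed threshold of 5 mg/dl. Patients enter because they need stenting, so a wide range of starting values can be expected. The CRP criterion in the endpoint refers partly to baseline; the bilirubin criterion does not. Nothing in the endpoint, the stratification or the model therefore takes account of the starting level.

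If the association is real, two things are at stake. First, a Cox model that includes a prognostic baseline value has more power for the treatment effect at the same sample size. Second, with 60 patients per arm, a chance difference in starting bilirubin would move the unadjusted hazard ratio, and the plan would only remark on it. Adding the covariate after such a difference had been seen would be post hoc in an open-label trial, so the choice belongs in the plan now.

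**Working it through.** **Inputs from the article (sample size paragraph).** "The sample size of 120, i.e., 60 patients per group"; the number "was calculated based on the two-sided log-rank test for time to first event analysis"; "the event rate at 6 months in the control group was estimated to be 50% and 25% in the intervention group". Also 80% power, two-sided 5%, fixed 6-month follow-up and 2.5% loss.

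**Step 1: reproduce the plan's figure.**

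- HR = ln(0.75)/ln(0.50) = 0.415, as stated.
- Expected events without loss: 60 × 0.50 + 60 × 0.25 = 45. With 2.5% loss: about 44.5.
- Log-rank test by the Lakatos method, exponential hazards, 2.5% loss: N = 116.0 for 80% power, and 81.3% power at N = 120.
- Comparison of two proportions: 58 per arm = 116; 116/0.975 = 119, or 120 with equal arms.
- Schoenfeld at 45 events: √(45/4) × |ln 0.415| − 1.96 = 0.99, power 83.9%.
- Freedman at 45 events: √45 × (1 − 0.415)/(1 + 0.415) − 1.96 = 0.81, power 79.2%.

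The stated 120 is reproduced with no covariate, so the planned power does not depend on adjusting for bilirubin.

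**Step 2: power with and without the covariate.** Simulation of 60 per arm, 3,000 trials per scenario. The hazard is λ(arm) × exp(bZ), with Z standard normal for standardized log bilirubin and b = ln(HR per SD). The arm hazards are set so that the overall 6-month rates stay at 50% and 25%. The HR per SD is **assumed**, because the article gives none.

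| Assumed HR per SD | Power without | Power with | Gain (points) | Median HR without / with |
|---|---|---|---|---|
| 1.0 | 81.5% | 81.5% | 0.0 | 0.412 / 0.410 |
| 1.25 | 81.3% | 82.2% | 0.9 | 0.410 / 0.406 |
| 1.5 | 81.2% | 83.8% | 2.6 | 0.411 / 0.396 |
| 2.0 | 81.9% | 88.4% | 6.5 | 0.415 / 0.375 |
| 2.5 | 80.4% | 91.6% | 11.2 | 0.408 / 0.342 |

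Monte Carlo error is about 0.7 points on each power. Under no treatment effect, rejection is 4.0–5.5% without the covariate and 4.6–5.4% with it. A second set of 4,000 simulated trials gives 81.5% without and 81.2% with a non-prognostic covariate, so the price of a useless term is negligible.

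**Step 3: let bilirubin act on only part of the endpoint.** Step 2 lets bilirubin drive every event, including cholangitis. Now assume that half of the hazard is unrelated to baseline bilirubin (4,000 trials). Power without and with the covariate is 82.0% and 82.9% at HR 1.5 per SD on the bilirubin part, 82.0% and 83.7% at 2.0, and 81.6% and 83.7% at 2.1. The gain falls to about 1 to 2 points.

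**Step 4: chance imbalance.** The standard error of the difference in mean Z between arms is √(2/60) = 0.183 SD. In the simulations of Step 2, the unadjusted log HR moves by 0.405 per SD of imbalance at HR 1.5 per SD, and by 0.622 at 2.0.

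- One standard error: exp(0.405 × 0.183) = 1.08 and exp(0.622 × 0.183) = 1.12. An HR of 0.415 would read 0.415 × 1.08 = 0.45 or 0.415 × 1.12 = 0.46 if the imbalance goes against RFA.
- 1.96 standard errors (0.36 SD): factors of 1.16 and 1.25, so 0.48 or 0.52.

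**Limits.** Site, tumor location, stent material and the competing event of death were not simulated, and the covariate effect is taken as correctly log-linear. The gains are approximate.

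**The case against.** The strongest reply is that nothing here is wrong. The model is prespecified, contains both stratification factors and agrees with the abstract, and the power claim holds without bilirubin. That stands. The article's silence on its reasons is also no fault, since a condensed article commonly leaves rationale to the full protocol or SAP.

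It is also fair that the outcome is not bilirubin as such. It is a biliary event by either of two limbs with a clinical consequence, reviewed by a blinded committee. The baseline sample precedes a stenting that is meant to relieve the obstruction. Patients may enter at a first stent or at a first replacement, so the same value can mean different things. The abstract speaks of an increase to above 5 mg/dl, and the strength of the link may depend on how that limb is read. The article itself says that data on prognostic factors in CCA are rare. All of this limits the likely gain, as Step 3 shows, and a single log-linear term may not fit perfectly.

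Two stronger readings are tempting and not supported:

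- A reader might infer that the trial is underpowered or is certainly giving power away. Step 1 shows that the plan meets its target, and the size of any gain rests on an unstated association.
- A reader might infer that the unadjusted hazard ratio is biased. Its lying closer to 1 than the adjusted one is non-collapsibility: the two models estimate different quantities, and the unadjusted one recovers the design value. Chance imbalance is sampling variation that the confidence interval already covers.

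What the reply does not show is that adjustment would do harm, or that the article deals with starting bilirubin elsewhere.

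**Conclusion.** The point holds as a recommendation for efficiency and robustness, not as an error or contradiction. The article does fix the covariates of its only confirmatory analysis, and it leaves out a scheduled pre-procedure value of a quantity that underlies one endpoint limb. The benefit is uncertain: about 0 to 3 points of power for an HR per SD of 1.0 to 1.5, about 7 to 11 points for 2.0 to 2.5 if all events are affected, and about 1 to 2 points if only the bilirubin limb is. These figures rest on assumed prognostic strengths and, for the last, on an assumed half share of the hazard. The trade is favorable because the loss is negligible if bilirubin turns out not to be prognostic.

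**What to change.** In the statistical analysis section, add log-transformed total bilirubin, from the last sample before the index procedure (screening or Visit 1), as a prespecified continuous fixed effect in the primary cause-specific Cox model and in the Fine and Gray analysis. This point leaves the site frailty, tumor location and stent material as planned. Report the model without bilirubin as a sensitivity analysis.

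The cost is one sentence and no new data. There are three downsides:

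- One more parameter is estimated from about 45 expected events.
- The adjusted hazard ratio is conditional on bilirubin and so not directly comparable with the design value of 0.415.
- Missing values are not to be imputed, so a patient without a baseline bilirubin would drop out of the adjusted model. Few should, given the schedule, and the sensitivity analysis keeps them.

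The change should be made before any outcome data by arm are seen.

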**Methods/Design:**

ACTICCA-2 is a multicenter, randomized, controlled, open-label, investigator-initiated trial. 120 patients with perihilar or ductal CCA with indication for biliary stenting and systemic therapy will be randomized 1:1 to receive either RFA plus bile duct stenting (interventional arm) or bile duct stenting alone (control arm). Patients will be stratified by trial site and tumor location (perihilar vs. ductal). Both arms receive palliative systemic treatment according to the local standard of care determined by a multidisciplinary tumorboard. The primary endpoint is time to first biliary event, which is determined by an increase of bilirubin to > 5 mg/dl and/or the occurrence of cholangitis leading to premature stent replacement and/or disruption of chemotherapy. Secondary endpoints include overall survival, safety according to NCI CTCAE v5, quality of life assessed by questionnaires (EORTC QLQ-C30 and QLQ-BIL21), clinical event rate at 6 months after RFA and total days of over-night stays in hospital. Follow-up for the primary endpoint will be 6 months, while survival assessment will be continued until end of study (maximum follow-up 30 month). All patients who are randomized and who underwent endoscopic stenting will be used for the primary endpoint analysis which will be conducted using a cause-specific Cox proportional hazards model with a frailty for trial site and fixed effects for the treatment group, tumor location, and stent material.

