### Arm A (intraductal RFA plus biliary stenting)

Patients assigned to the study arm will receive systemic treatment and bile duct stenting with plastic or metallic stents with intraductal RFA of malignant bile duct obstructions employing a CE-certified RFA-catheter prior to stent placement. RFA will be applied once.

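### The confirmatory Cox model and the OS model adjust for stent material, which is realised after randomization; unless it is fixed before allocation or independent of arm, the adjusted HR may not estimate the effect of randomized assignment

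*Protocol article*

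**What the plan says.** All references are to the protocol article.

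- **Primary model** (Sample size calculation and statistical analysis): a cause-specific Cox model with a site frailty and "tumor location (perihilar vs. ductal) and stent material (plastic vs. metallic) as fixed effects". The abstract repeats this as "fixed effects for the treatment group, tumor location, and stent material". The primary endpoint is the only confirmatory analysis, at two-sided 5%.
- **OS model** (same section): Cox with a site frailty, "adjusting for stratification variable tumor location and the variable stent material". This wording itself separates the stratification variable from stent material. OS is exploratory.
- **Randomization** (Patient selection and randomization): 1:1, stratified by site and tumor location only, on the day of the procedure.
- **Arms**: arm A receives "bile duct stenting with plastic or metallic stents with intraductal RFA of malignant bile duct obstructions", with the ablation coming before the stent. Arm B may also receive either material. No selection rule is given for either arm.
- **Blinding** (Quality assurance and safety): the article acknowledges that investigators know whether RFA was done. The blinded committee reviews events.
- **Recording**: neither Table 2 nor the screening and visit 1 lists include an intended stent material.
- **Sensitivity analyses**: Fine and Gray, and per protocol. None without stent material is described.

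**The concern.** Adjusting for a baseline covariate in a randomized comparison is harmless and often helpful. Adjusting for something realised after allocation is different, because the variable may depend on the arm. Two things can then go wrong.

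1. If RFA changes which stent is placed, and material affects patency, the stent term removes the part of the assignment effect that runs through stent choice.
2. If an unmeasured feature such as stricture severity influences both stent choice and biliary events, comparing arms within stent material compares patients who are no longer alike, and a spurious treatment effect can appear.

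The trial's single confirmatory HR, confidence interval and p-value come from this model. The covariate is also loosely defined: event-free patients may have the stent replaced at visits 2 and 3, and the article does not say which stent's material enters the model.

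**Working it through.** **1. The plan's own figure.** The article states "The sample size of 120, i.e., 60 patients per group, was calculated based on the two-sided log-rank test", with event rates of "50% and 25% in the intervention group resulting in a hazard ratio (HR) of 0.415", 80% power, two-sided 5%, 6 months' fixed follow-up and 2.5% loss.

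- HR = ln(0.75)/ln(0.50) = 0.415, as stated.
- Mean event probability = (0.50 + 0.25)/2 = 0.375, so 120 × 0.375 = 45 expected events.
- Freedman's formula: 46 events, 46/0.375 = 123 patients. Power at 120 patients is 79.2% without loss and 78.7% with it.
- Schoenfeld's formula: 41 events, about 110 patients.
- Two proportions: 58 per arm, 58/0.975 = 59.5, rounded up to 60.

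The 120 reproduces and involves no covariates, so the sample size is not at issue.

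**2. When the covariate is realised.** Randomization comes first and the procedure follows the same day. In arm A the order is RFA, then stent. Material is therefore realised after allocation in both arms, and after RFA in arm A.

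**3. How far the two HRs can differ.** The article gives no metal-stent share and no effect of material, so these are assumptions, shown over a range. Event times are exponential and cut at 6 months, with 2.5% loss. The control hazard is ln(2)/6 = 0.1155 per month, divided by 0.8 because 0.6 × 1 + 0.4 × 0.5 = 0.8 at 40% metal with HR 0.5. HRs come from 400,000 simulated patients, and rejection rates from 3,000 trials of 120.

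Metal-stent HR 0.5, stent choice unrelated to prognosis:

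| Direct RFA HR | Metal share, control / RFA | HR without stent term | HR with stent term | Rejection rate, without / with |
|---|---|---|---|---|
| 0.415 | 40% / 40% | 0.42 | 0.415 | 79.5% / 81.4% |
| 0.415 | 40% / 60% | 0.37 | 0.42 | 87.6% / 76.6% |
| 0.415 | 40% / 20% | 0.48 | 0.41 | 67.4% / 81.0% |
| 1 | 40% / 60% | 0.87 | 1.00 | 8.5% / 5.4% |

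**4. Confounded stent choice under a complete null.** RFA and material both have no effect. An unmeasured factor present in half the patients has HR 3 and moves the chance of a metal stent by ±35 percentage points.

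| Metal share, control / RFA | HR without / with stent term | Type I error, without / with |
|---|---|---|
| 40% / 40% | 1.00 / 1.00 | 5.4% / 5.0% |
| 40% / 60% | 1.00 / 0.86 | 4.6% / 8.9% |
| 35% / 65% | 1.00 / 0.78 | 4.8% / 14.1% |
| 40% / 60%, factor acts on choice in RFA arm only | 1.01 / 0.95 | 4.5% / 5.3% |

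A further run with different confounding assumptions and competing death (assumed median 11.5 months) gave adjusted HRs of 1.08 to 1.13 and type I error of 6 to 7%. The direction therefore depends on the confounding pattern.

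The tabulated runs omit the site frailty, tumor location and competing death. They show direction and rough size only.

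**The case against.** **The documents do not say who chooses the material, or when.** A reader might infer that an unblinded endoscopist picks the stent after seeing what RFA did to the stricture. The article leaves the RFA device and the extent of ablation to the investigator but says nothing about who chooses the stent material. It fixes only when the stent is placed. The design figure, not available here, has a legend that mentions metal stents and may bear on this. This objection stands.

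**The adjusted HR is not necessarily wrong.** A reader might conclude that the reported HR is not the randomized treatment effect. That is too strong. With equal shares by arm the two HRs practically agree (0.42 and 0.415), and the small gap is non-collapsibility.

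**The shift need not decide the trial.** With 45 events, significance needs an observed HR of about exp(−1.96 × 2/√45) = 0.557 or lower. All the planned-effect pairs above (0.42/0.415, 0.37/0.42, 0.48/0.41) lie below that. What changes is power, and under confounding the type I error.

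**Planned or placed material is SAP detail.** In part it is, and the model as written is compatible with a pre-randomization value. But the protocol names the covariate for the confirmatory test, and nothing in it secures independence from arm.

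**The objective is the efficacy of RFA, so a direct effect may be wanted.** With no direct effect and 40%/60% shares, the unadjusted HR of 0.87 reflects stent mix alone. This is a fair estimand argument. However, the stated objective compares RFA before stenting with stenting alone, and randomization protects that comparison of assignment. Reading the stent-adjusted HR as a direct effect needs the untestable assumption of no unmeasured common cause of stent choice and events.

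**An imbalance would be visible.** Material must be recorded to enter the model, so it can be tabulated by arm, and cumulative incidences are reported with no stent adjustment stated. Both help to detect a problem, but neither corrects the confirmatory p-value.

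**Conclusion.** The concern holds in conditional form. The confirmatory model, and the exploratory OS model, condition on a non-stratified variable realised after randomization and, in arm A, after RFA, with open allocation and no stated pre-randomization recording. The adjusted HR may therefore not estimate the effect of randomized assignment unless material is fixed before allocation or is independent of arm.

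Under the assumed metal-stent HR of 0.5 and direct RFA HR of 0.415, the difference is negligible at equal shares and about 0.05 to 0.07 on the HR scale for a 20-point difference in metal share, in either direction. Under confounded choice with unequal shares, type I error was about 6 to 14% in the patterns where it rose; in one pattern it stayed near 5%. None of these shares or effects comes from the documents.

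The point matters most for the primary analysis. For OS it affects interpretation only.

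**What to change.** - In the primary and OS models, adjust only for the randomization factors (site frailty and tumor location). Alternatively, use the intended stent material, entered in the eCRF before randomization, and state that this is the covariate.
- Report the model with the material actually placed as a sensitivity or exploratory analysis, and say which stent it refers to.
- Tabulate stent material by arm.

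**Cost:** a wording change in the protocol and SAP, one eCRF field if intended material is used, and slightly less explained variance. The planned 120 patients stay as they are. If the intended material is to be used, the field should be in place before recruitment, because a pre-randomization value cannot be recovered for patients already randomized.

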More recently, three randomized controlled trials were reported. Most recently, a multicenter study including patients with CCA and pancreatic cancer with malignant biliary obstruction by Jarosova et al. (2023) compared endoluminal RFA plus stenting and stenting alone. In this study, OS did not differ significantly between the RFA group and the control group among patients with CCA (10.5 vs. 10.6 months, *n* = 85, *p* = 0.58), and no benefit was seen in the RFA group with regards to stent patency (40% vs. 36% at 12 months), quality of life, and adverse event rate [6]. The study was therefore prematurely terminated due to futility. Noteworthy, the RFA group contained more patients with distal CCA (18% vs. 10%), which is considered to have a worse prognosis compared to hilar CCA, and less patients with concomitant (9% vs. 20%) or adjuvant (20% vs. 37%) anti-cancer therapy rendering a potential bias in the survival analysis. In contrast, studies by Gao et al. and Yang et al. reported improved OS when comparing RFA plus stenting vs. stenting alone. Gao et al. performed a multicenter randomized trial, including 47 patients with hilar CCA and 100 patients with distal CCA, and reported an OS of 13.3 months in the RFA group vs. 9.2 months in the control group (hazard ratio 0.546, *p* < 0.001). However, no significant differences were found regarding jaundice control or stent patency duration between the groups [7]. Noteworthy, this study was limited to patients who were not eligible for systemic therapy, thus reflecting a different patient population compared to our study design. In line with this, Yang et al. performed a single-center randomized trial in patients with perihilar or distal CCA (*n* = 65) and reported an OS of 13.2 vs. 8.3 months (*p* < 0.001) for RFA plus stenting vs. stenting alone [9]. However, the latter trial did not include data on systemic chemotherapy as SOC in these patients. In conclusion, evidence is scarce and inconsistent and thus comparing RFA plus stenting vs. stenting alone in the context of systemic chemotherapy in patients with unresectable CCA is strongly required.

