No concomitant disease or malignancy interfering with the study procedure or efficacy outcome measures, particularly no severe or uncontrolled cardiovascular disease (congestive heart failure NYHA III or IV, unstable angina pectoris, myocardial infarction within ≤ 3 months, significant arrhythmias) and no psychiatric disorders precluding understanding of information of trial related topics and giving informed consent

*CCA*: cholangiocarcinoma, *ECOG*: Eastern Cooperative Oncology Group, *RFA*: radio frequency ablation, *NYHA*: New York Heart Association Functional Classification, *MDT*: multidisciplinary team

Randomization to study treatment should occur within three weeks after eligibility criteria have been met. Study subjects will be randomized by the electronic CRF to arm A (intervention group) or B (control group) in 1:1 ratio, stratified by trial site and tumor location (perihilar vs. ductal). The procedure itself (i.e., endoscopic stenting with or without RFA) and randomization are on the same day.

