#### Randomization and treatment (visit 1)

After enrolment, patients will be randomized (1:1) to either receive intraductal RFA followed by bile duct stenting or bile duct stenting alone. Additionally, the following will be assessed for baseline:

Laboratory tests as shown above (only if screening lab values are > 7 days old).Safety (terminology and grading according to NCI CTCAE v5 [see suppl. material])Data collection regarding administration and complications of systemic therapy (administered as SOC).Quality of life (QoL) assessment using the European Organisation for Research and Treatment of Cancer (EORTC) questionnaire QLQ-C30 [see suppl. material Fig. 1] and the module BIL21 [see suppl. material Fig. 2].

#### Visit 2 & 3

The following will be assessed at three and six months (each +/- 2 weeks) after randomization:

Laboratory tests as shown above.ERCP and stent replacement (within regular clinical management of the patients), not mandatory for patients who have experienced the primary endpoint of stent dysfunction, resulting in a change of timeline regarding stent replacement.Safety, data collection regarding administration and complications of systemic therapy (SOC), QoL, days of overnight hospital stays, and survival status.

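### The OS Cox model omits ECOG and systemic-therapy status at entry, both already collected, so chance imbalance in either can move the exploratory OS hazard ratio

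*Protocol article*

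**What the plan says.** Under Sample size calculation and statistical analysis, the protocol article does not leave the OS covariates open. It specifies a Cox model "with a frailty for trial site and adjusting for stratification variable tumor location and the variable stent material". Randomisation is "stratified by trial site and tumor location (perihilar vs. ductal"), so the model covers both stratification factors and adds stent material.

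Two further patient-level factors are available at entry:

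- **ECOG.** It is listed among the screening items and limited by eligibility to two levels: "Performance status 0–1 according to the Eastern Cooperative Oncology Group (ECOG) is a well-established cut-off for the eligibility of patients".
- **Systemic therapy.** The Visit 1 baseline list includes "Data collection regarding administration and complications of systemic therapy (administered as SOC"). Screening also records "Medical history including previous cancer history, cancer treatment, concomitant diseases, current medication, prior endoscopic procedures".

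The statistical section rules out significance tests on baseline characteristics and says that the clinical importance of an imbalance will be noted. It names no adjusted analysis that would follow. OS is secondary, has no stated power or event target, and belongs to the analyses declared exploratory.

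**The concern.** ECOG and treatment status at entry are plausible prognostic factors for survival. They are measured before or at randomisation and cost nothing more to use. With 60 patients per arm, randomisation that is not stratified on them will often leave visible differences between arms. An OS model without them attributes part of such a difference to RFA. If the trial team adds the covariates only after seeing the imbalance, the adjusted result carries less weight than a pre-specified one.

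Status at entry can vary. The Background describes stenting before and during chemotherapy. Eligibility allows entry at initial stent placement or at first stent replacement. Systemic therapy is given outside the trial by local standard. The authors are alert to this type of problem: of an earlier randomised trial they write that its RFA arm had "less patients with concomitant (9% vs. 20%) or adjuvant (20% vs. 37%) anti-cancer therapy rendering a potential bias in the survival analysis".

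What is at stake is the credibility of the trial's comparative survival estimate, not its confirmatory conclusion.

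**Working it through.** **1. The plan's own figure (primary endpoint).** Inputs from the sample size section: 50% vs 25% events at 6 months, 60 per arm, two-sided 5%, 2.5% loss.

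- HR = ln(0.75)/ln(0.50) = 0.415, as stated.
- Power at N = 120: 81.3% by a log-rank non-centrality calculation. With about 44.5 expected events it is 83.5% by Schoenfeld and 78.7% by Freedman.

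The stated 80% is reproduced, and this point does not affect it. There is no OS power figure to reproduce.

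**2. How large is chance imbalance?** The prevalence q of each factor is not in the documents; 40% is assumed.

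- SD of the difference in proportions = √(q(1−q)·2/60) = √(0.4·0.6·2/60) = 0.089, or 8.9 percentage points.
- P(difference of 10 points or more) = 2·(1−Φ(0.10/0.0894)) ≈ 26%.
- At q = 30% or 50% the SD is 8.4 or 9.1 points, so the result depends little on q.

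**3. How far does one factor move the OS HR?** Approximate shift = exp(imbalance × ln(factor HR)). A 1.96-SD imbalance is 1.96 × 0.0894 = 0.175. The factor HRs are assumed.

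| Assumed factor HR | Calculation | Shift in OS HR |
|---|---|---|
| 1.3 | exp(0.175 × 0.262) | 1.05 |
| 1.5 | exp(0.175 × 0.405) | 1.07 |
| 2.0 | exp(0.175 × 0.693) | 1.13 |

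**4. Both factors together, and power.** Cox fits were simulated with and without two binary factors. Assumptions: 120 patients, control median OS about 10.6 months (the control-arm figure for CCA patients that the article quotes from an earlier randomised trial), censoring uniform from 6 to 30 months, prevalence 40% each. Site, tumour location and stent material were left out for simplicity. At true OS HRs of 0.6 and 0.7 this gives about 69 and 72 deaths.

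| True OS HR | Factor HRs | Power without | Power with |
|---|---|---|---|
| 0.6 | 1.3, 1.3 | 54.6% | 56.9% |
| 0.6 | 1.5, 1.5 | 53–54% | 56–57% |
| 0.6 | 2.0, 2.0 | 48–49% | 55–56% |
| 0.6 | 2.0, 2.5 | 45.2% | 54.4% |
| 0.7 | 1.3, 1.3 | 31.7% | 32.4% |
| 0.7 | 1.5, 1.5 | 29.7% | 30.3% |
| 0.7 | 2.0, 2.0 | 27.2% | 30.0% |

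The loss is about 1 to 3 points at factor HRs of 1.3 to 1.5 and about 3 to 9 points at 2.0 or more. At a true OS HR of 0.5 the strongest pair gives 10 points (68.8% vs 78.8%).

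The standard error does not shrink with adjustment: at true OS HR 0.6 and factor HRs of 2.0, the SD of the log HR is about 0.245 without and 0.253 with the factors. The gain comes from removing attenuation; the average HR in that scenario is 0.62 unadjusted and 0.59 adjusted.

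The SD of the difference between unadjusted and adjusted log HR is about 0.06, 0.08 and 0.11 for factor HRs of 1.3, 1.5 and 2.0. For comparison, it is 0.04 when the factors have no effect, and the sampling SD of the log HR is about 0.24.

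**5. Type I error.** With a true OS HR of 1.0, the model without the factors rejects in 4.5–5.3% of simulated trials.

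**The case against.** The other side has a good case, and much of it stands.

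- **Planning figure for later trials.** A reader might infer that a distorted HR is handed to the next trial. The Endpoint definition section names median OS for that purpose, and Cox covariates do not change an arm's estimated median.
- **Bias towards the null.** A reader might call the unadjusted HR biased. The two HRs answer different questions, because the Cox HR is non-collapsible. A later trial sized on an unadjusted log-rank test, as this one was, would want the marginal HR. The null test keeps its level.
- **Power.** OS is exploratory and has no power target. Gains beyond about 3 points need both factors near HR 2. The documents give no such figure, and the Study rationale says that data on prognostic factors are scarce. ECOG limited to 0–1 also has little spread.
- **The same imbalance as in the earlier trial.** That criticism concerned therapy received. Here eligibility for systemic therapy is required and all patients are to receive it, so the proposed covariate captures whether it had begun at entry. The passage shows that the authors take such imbalance seriously; it does not show that this trial repeats it.
- **Convention and the SAP.** Adjusting for the stratification factors is a normal choice, and supplementary analyses may sit in the SAP that the article announces.

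The last argument does not remove the point. The article fixes the main OS model by name, goes beyond the stratification factors for stent material, and leaves out two baseline patient factors that it collects.

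**Conclusion.** The point holds as a minor one. The OS model omits two available baseline factors, and chance imbalance in one of them can move the OS HR by roughly 5–13%. This rests on assumed factor HRs of 1.3 to 2.0, prevalence near 40%, and an imbalance at the 1.96-SD limit.

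A reader might quote a shift of 1.2 or more (1.96 × 0.11 = 0.22 on the log scale, a factor of about 1.24). That is a tail value for two factors both at HR 2.0, and part of it is estimation noise. The documents do not support it as a typical size.

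Nothing here affects the primary analysis, the sample size, type I error or the median OS estimates.

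**What to change.** In the OS sentence of Sample size calculation and statistical analysis, pre-specify two additional fixed effects: ECOG (0 vs 1) and systemic therapy before randomisation (not started vs already started). State that site frailty, tumour location and stent material stay as listed. Define the therapy covariate by its value before randomisation only. Therapy given afterwards can be affected by allocation and lies on the pathway that the Study rationale proposes. If the main model is to stay as it is, name the extended model as a sensitivity analysis before the data are seen.

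The cost is one sentence, with no new data and no more patients. The downside is two more parameters for about 67 to 72 deaths (under the assumed survival) and an HR that is conditional on these factors. The report should say so when comparing it with unadjusted results from other trials.
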